## Abstract

**Background:**

Whilst schools provide a potentially appropriate setting for preventing substance use among young people, systematic review evidence suggests that past interventions in this setting have demonstrated limited effectiveness in preventing tobacco, alcohol and other drug use. Interventions that adopt a mental wellbeing approach to prevent substance use offer considerable promise and resilience theory provides one method to impact on adolescent mental well-being. The aim of the proposed study is to examine the efficacy of a resilience intervention in decreasing the tobacco, alcohol and illicit drug use of adolescents.

**Methods:**

A cluster randomised controlled trial with schools as the unit of randomisation will be undertaken. Thirty two schools in disadvantaged areas will be allocated to either an intervention or a control group. A comprehensive resilience intervention will be implemented, inclusive of explicit program adoption strategies. Baseline surveys will be conducted with students in Grade 7 in both groups and again three years later when the student cohort is in Grade 10. The primary outcome measures will include self-reported tobacco, alcohol, marijuana and other illicit drug use. Comparisons will be made post-test between Grade 10 students in intervention and control schools to determine intervention effectiveness across all measures.

**Discussion:**

To the authors’ knowledge this is the first randomised controlled trial to evaluate the effectiveness of a comprehensive school-based resilience intervention, inclusive of explicit adoption strategies, in decreasing tobacco, alcohol and illicit drug use of adolescents attending disadvantaged secondary schools.

**Trial registration:**

ACTRN12611000606987

## Background

Globally, a significant proportion of people, including those in Australia, are at risk of harm from smoking, alcohol misuse or illicit drug use [1,2]. Of all age groups, young people report the greatest prevalence of such substance use [3]. The younger the age of initiation of substance use, the greater the likelihood of ongoing use, dependence and harm in later life [4]. As such, primary prevention efforts focusing on preventing initiation of substance use by young people have been recommended [5].

Schools provide an appropriate setting for improving the immediate and long term health of young people as adolescents [6-8], however there is limited evidence that school-based programs are effective [5,9,10]. A recent review of school-based programs targeting alcohol however has reported that interventions that aimed to develop the psychological or social skills of young people had the most promise [5,9]. The findings of these reviews are consistent with a World Health Organisation review that concluded that programs that promote young people’s mental well-being were most likely to be effective [11]. The same World Health Organisation review suggests that school-based interventions that address the school curriculum, school environment and community were the most likely to achieve a beneficial outcome, a method known as the Health Promoting Schools approach [11].

Resilience theory, which has arisen from the study of risk factors for, and their impact on, positive youth development represents one approach to improving adolescent mental or psychosocial well-being [12-18]. Whilst there is variation in the definition of resilience, it is generally agreed that both individual (internal) as well as environmental (external) characteristics contribute to individual resilience and are critical for positive youth development and the avoidance of risk behaviours [19-21]. An inverse association has been found to exist between adolescent resilience characteristics and substance use [22-24].

Although a number of school-based studies have reported targeting some aspect of adolescent resilience as a basis for intervention, none have applied the approach in a comprehensive manner nor have they demonstrated consistent effect [25-30]. In a number of such studies, the researchers have concluded that inadequate intervention dose and fidelity may have contributed to the limited outcomes [29]. A number of barriers to intervention adoption have been cited including: a lack of financial resources for planning, training, and teacher release; inadequate levels of professional development; inadequate program resources; failure to adopt a ‘whole of school’ approach to implementation and monitoring; and inadequate support by school executives [31].

A pilot study of a comprehensive intervention addressing both internal and external adolescent resilience factors in a convenience sample of three socio-economically disadvantaged secondary schools has recently been reported. The intervention was delivered using the Health Promoting Schools approach [32], and included explicit strategies to enhance intervention adoption such as adoption support staff, resource provision and staff training. The evaluation suggested significant increases across all three schools in internal and external resilience scores, and significant decreases across all three schools in prevalence of student smoking, alcohol consumption and marijuana use [32]. Such positive outcomes were demonstrated for all grades and genders, and exceeded declining temporal trends in the broader population [32].

Whilst the findings of the pilot study were positive, a more rigorous study design is required to confirm the potential of such a comprehensive resilience enhancing approach. A cluster randomized controlled trial is planned to examine the efficacy of a comprehensive resilience intervention, inclusive of intervention adoption strategies, in decreasing the tobacco, alcohol and illicit drug use of adolescents attending secondary schools in a socio-economically disadvantaged region.

## Methods

### Study design

A cluster randomised control trial design (Figure 1) will be conducted, with schools as the unit of randomisation. Thirty two schools will be randomly selected to participate in the study, with 20 schools randomly allocated to the intervention group, and 12 to the control group. A resilience intervention will be implemented in schools allocated to the intervention group. Schools allocated to the control group will not receive any intervention during the study period. To assess the efficacy of the intervention, baseline web-based surveys will be conducted with Grade 7 students. Follow up data will be collected using the same method three years later when the original cohort of students are in Grade 10.

**Figure 1 F1:**
[figure not shown]
Estimated CONSORT flow diagram of the school progress through the phrases of the trial.

The trial has been approved by the Hunter New England Health Human Research Ethics Committee (Ref no. 09/11/18/4.01), The University of Newcastle Human Research Ethics Committee (Ref no. H-2010-0029), the Aboriginal Health and Medical Research Council (Ref no. 776/11), the New South Wales Department of Education and Training State Education Research Approval Process (Ref no. 2008118), and the relevant Catholic Schools Offices. In addition, the trial is registered with the Australia and New Zealand Clinical Trials Register (Ref no. ACTRN12611000606987).

### Participants

#### School sample

The study will be conducted in 32 government and Catholic secondary schools within the Hunter New England Local Health District of New South Wales, Australia. Approximately 135,000 adolescents reside in the Hunter New England Local Health District which encompasses metropolitan, regional, rural and remote locations across an area of 130,000 square km [33].

Schools will be selected from a list of all government and Catholic secondary schools in the study area obtained from the Department of Education and Training and from relevant regional Catholic School Offices. Schools will be eligible if they are located in a disadvantaged Local Government Area (as defined by the SEIFA Index of Relative Socio-Economic Advantage/Disadvantage by Local Government Area) [34], have more than 400 total student enrolments, and have enrolments in Grades 7 to 10. In addition, due to the likelihood of differential effects, schools which are entirely special needs or selective, central schools, boarding schools or are not co-educational schools are ineligible for inclusion in the trial.

#### School recruitment

Before being invited to participate in the trial, briefing meetings will be held to inform all school principals of the study. An eligibility interview will subsequently be conducted with each school principal to identify current implementation of resilience strategies. Schools considered to be implementing a comprehensive resilience intervention within each domain of the Health Promoting Schools framework across all grades will be ineligible and removed from the list of eligible schools.

The order in which eligible schools will be invited to participate will be determined using a random number function (in Microsoft Excel) by an independent statistician. The principals of the first 32 randomly selected eligible secondary schools will be sent a letter informing them about the study and requesting written consent for their school to participate. Within one week from the initial information letters being sent, research staff will contact non-responding principals to answer any questions they may have and to prompt their reply. Principals that do not reply within a further week will receive additional prompts from research staff. If a school declines to consent the next school on the list will be invited, following the same procedure above.

#### Random allocation of schools

Once 32 schools have been recruited to the study, the sample will be stratified by engagement in a national government initiative directed at schools in disadvantaged areas [35], and school size (medium sized school 400–800; large sized school >800). Schools will then be randomly allocated in a 20:12 block design ratio to either the intervention or the control group. Neither schools, parents of students, nor students attending selected schools will be blinded to the school allocation.

#### Student sample

All students in Grade 7 (first year at high school and aged 12 to 13 years) attending consenting schools will be eligible to participate in the study (approximately 3,600 students at baseline).

#### Student recruitment

Active parental consent will be required for child participation in the evaluation component of the study. A number of strategies will be employed to maximize parental consent for child participation based on a recent review of school-based recruitment methods [36]. Schools will be provided with information to disseminate via existing school communication channels, including school newsletters, assemblies, staff meetings, and school community and parent meetings. Parents of children will be mailed study information packs that include a short cover letter from the school principal on school letterhead, a detailed study information letter for parents, a simplified study information letter for students, a parental consent form for child participation in the study and a reply paid envelope. The information letter will also provide the details for a free call message service on which parents can leave their details if they do not want to be prompted for consent. Parents will be asked to return the consent form by either using the reply paid envelope or by providing it to their child’s school.

Two weeks after distribution of the information packs, non-responding parents will be telephoned by school affiliated staff to prompt return of the child consent form. During the phone call, parents will be asked if they consent to their child participating in the survey. Parents who provide verbal consent during this phone call will be mailed a replacement information sheet and consent form (with reply paid envelope) so that written consent can be obtained.

### Resilience intervention

#### Intervention content

A multi-strategy intervention, based on a range of programs and strategies that address both internal and external adolescent resilience factors will be implemented for the whole school. Schools will be asked to implement a range of strategies in each of the Health Promoting Schools domains (curriculum, teaching and learning; ethos and environment; and partnerships and services) to enhance student resilience [37]. The strategies schools select will be informed by a comprehensive and structured planning process and will be selected from a list of evidence based programs (eg. MindMatters program). In this manner, the strategies implemented by each school may differ. However, schools will be asked to implement strategies to an intervention standard (see Table 1).

**Table 1 T1:** Resilience intervention standards

**Curriculum, teaching and learning**	
·	100% of students in Grade 7-10 receive a minimum of 12 age-appropriate resilience lessons across subjects (e.g. implementation of MindMatters curriculum resources) [38]
·	100% of students in Grade 7-10 receive an additional 9 hours of non-curriculum based resilience programs (e.g. implementation of the ‘Resourceful Adolescent Program [34]
**Ethos and environment**	
·	Rewards and recognition program implemented across the whole school
·	Peer support/peer mentoring programs implemented across the whole school
·	Anti-bullying programs implemented across the whole school
·	Cultural awareness program implemented across the whole school
·	Teacher offered training to implement effective pedagogy within learning environments (e.g. MindMatters Teaching and Learning for Engagement) [38]
**Partnerships and services**	
·	Promotion and engagement of local community organisations/groups/clubs in the school (e.g. charity organisations, church or sporting groups)
·	Promotion and engagement of health and community services in the school (e.g. Youth and Child and Adolescent Mental Health Services)
·	School implement strategies to increase parental involvement in school (e.g. school events, effective parent communication strategies)
·	School promotes strategies to address students resilience at home (e.g. newletters regarding enhancing student resilience)

### Intervention adoption strategies

To increase the extent of intervention adoption and fidelity across schools, a number of strategies will be implemented that have been previously reported to facilitate adoption of school-based interventions, to change the service delivery practices of human service organizations, and to build capacity of organisations [17,31,39-44].

#### School intervention officers

A part-time school intervention officer will be located in each school to support data collection, and program planning, implementation and monitoring. Their role will be to support schools to implement the resilience intervention. School intervention officers will not implement intervention strategies directly with students. Such officers will be employed for three years and allocated to intervention schools at a ratio of one officer per four schools. Prior to intervention implementation, school intervention officers will undertake a two week intervention training program.

A school project coordinator will be employed full time for two years to support the implementation of the intervention at a regional level, provide support to the school intervention officers, and liaise with schools and the two education sectors.

#### Fiscal resources

In each year of the intervention, schools will be provided with an annual allocation of AUS$2,000 seed funding to facilitate training, professional development and teacher release time for intervention implementation.

#### Leadership

A school core team will be established, or an existing team will be enhanced, at each school to lead the implementation of the project. The core team will include the allocated school intervention officer, school staff and involvement of at least one member of the school executive.

#### Structured planning process

A structured planning process will be undertaken to design and implement the intervention in each school. A needs assessment will be undertaken immediately prior to intervention implementation to inform the development of strategies targeting student resilience. This assessment will include a resilience factor and substance use survey of all students in Grades 7 to 10 and a school environment survey of school policies, practices and curriculum that may impact on student resilience.

Planning workshops will then be held at each school to prioritize student resilience needs and identify feasible strategies to address them. Following this, each school will develop an individual intervention plan which will be endorsed by the school executive and integrated into existing student welfare governance processes and school planning. Schools will be provided with an implementation guide that describes in detail the steps required to implement this planning process, inclusive of available resilience programs, tools and templates.

#### Training

Key school staff will be provided with training in the planning, delivery and monitoring of the resilience intervention strategies (including resilience professional development). All school staff will be offered training in effective pedagogy for enhancing student resilience [45], and mental health literacy [46].

#### Monitoring and feedback

The school intervention officer will be responsible for monitoring and maintaining project records. School-specific feedback regarding intervention progress and data collected via student surveys will be provided to each. Intervention progress will also be provided to senior managers from the New South Wales Department of Education and Training and the relevant regional Catholic School Offices.

### Control group

Schools allocated to the control group will receive a report of their student survey data in the first and fourth year of the study. In addition, control schools will be given all printed intervention resources at the conclusion of the trial.

### Data collection procedures

#### Student outcomes

Baseline data will be collected via a student survey completed by all consenting students in Grade 7 in both intervention and control schools in the first year of the study. Follow up data will be collected from the same students in the fourth year of the study when the student cohort is in Grade 10 in the same season as baseline.

The student survey will take approximately 25 minutes to complete. Data collection staff will be recruited and trained to support students to complete the online survey during class time.

#### School outcomes

At baseline and follow up, a school environment survey will be undertaken with key school staff including principals and head teachers of both intervention and control schools to identify existing school policies and practices that target student resilience.

### Measures

#### Student demographics

The student survey will include the following demographic items: age, Grade, gender, ethnicity and Aboriginal and Torres Strait Islander status, languages spoken at home, and postcode.

#### Primary outcome measures – substance use

The outcome measures will be student-reported smoking, alcohol use and illicit drug use.

For both recent tobacco and alcohol use, retrospective diaries will be used to measure consumption in the past 7 days [25,47,48]. Recent use will be defined as having smoked any cigarettes or consumed any alcoholic drinks in the last week. These items are used regularly in Australian state-wide surveys of secondary school student health behaviours [49].

For risky alcohol consumption, the Australian guidelines recommend that there is no safe drinking level for adolescents [50]. As such, a measure of risky drinking based upon the Australian recommendations for adult risk for injury (no more than 4 standard drinks on one occasion) will be used [50].

For illicit drug use, data regarding marijuana and any other illicit drug use in the past month will be collected [49]. The items are used regularly in state-wide surveys of secondary school student health behaviours [49].

Data will also be collected regarding known moderators of tobacco and alcohol use, including sibling use, parent/carer use, access, receipt of pocket money or income from paid employment, and belief health will be damaged by tobacco and alcohol use [51,52].

In a selection of schools, a 10% random selection of students whose parents have provided consent will be asked to provide a saliva sample at the completion of the student survey in the fourth year of the study. The saliva sample will be used to test for the presence of cotinine (a metabolite of nicotine) to validate the accuracy of their self-reported tobacco use [53]. All students attending these schools will be informed that they may be selected to provide a saliva sample to confirm their smoking status (a variation of the bogus pipeline method) [54]. Although the accuracy of cotinine assessment may be influenced by less frequent adolescent smoking, it is the most suitable measure given its low level of personal intrusion, portability and cost [55].

#### Secondary outcome measures - resilience

Items from the California Healthy Kids Survey will be used to measure student internal and external resilience. The survey addresses six internal resilience factor subscales and eight external resilience factor subscales which have demonstrated adequate reliability [31]. The internal resilience subscales include Likert scale items addressing: cooperation and communication (2 items); self-efficacy (4 items); empathy (3 items); problem solving (3 items); self-awareness (3 items); goals and aspirations (3 items); school support (6 items); school meaningful participation (3 items); community support (6 items); community meaningful participation (3 items); home support (6 items); home meaningful participation (3 items); peer caring relationships (3 items); pro-social peers (3 items).

#### School environment survey

The school environment survey will be developed by the research team and will aim to measure the programs, curriculum, policies, practices, and partnerships that schools are currently implementing that target student resilience.

### Sample size

Based on past research [7,56], and the pilot study results, an estimated 80% of students will consent to participate. Based on this, and an estimated loss of students to follow-up from Grade 7 to Grade 10 of 25% a cohort sample of 1,360 Grade 7 students and 1,020 Grade 10 students in the control condition, and 2,270 Grade 7 students and 1,700 Grade 10 students in the intervention condition, will be the subject of analysis. Assuming 80% power, a 5% significance level, an intra-cluster correlation of 0.01, and a Grade 10 control group smoking prevalence of 14% the study will be able to detect a 4.8% lower prevalence of smoking for the intervention group. For recent and risky alcohol consumption, assuming a Grade 10 control group prevalence of 36.2%, a 7.0% lower prevalence of consumption can be detected. For use of marijuana, assuming a Grade 10 control group prevalence of 25%, a 6.2% lower prevalence of use respectively can be detected for marijuana. Finally, for other illicit drugs, assuming a Grade 10 control group prevalence of 9.3%, a 3.9% lower prevalence of use can be detected for the intervention group.

### Statistical analysis

All analyses will be undertaken using SAS Software Version 9.2 [57].

#### Demographic characteristics

Intervention and control school parental consent rates will be examined for non-response bias using Chi square analysis. Intervention and control school student demographic characteristics will be compared at baseline and follow up also using Chi square analysis.

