#### Primary outcomes – substance use

Comparisons in prevalence of substance use will be made between Grade 10 students in intervention and control schools at follow up to determine intervention effectiveness for each outcome measure. Generalized linear models (generalized estimating equation (GEE approach)) will be used [58]. The GEE will cater for dichotomous outcome data, school clustering, levels of strategy implementation, and student or school characteristics that are potential confounding variables. Usual assumptions of linear regression will be tested (including linearity, independence, constant variance and normality), with variations from normality adjusted for using the robust variance estimator. For all outcome analyses, school will be included in the model as the clustering unit.

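### Consent rates and student demographics are compared between arms by chi-square with no stated allowance for school clustering, so the check on non-response bias has an inflated false-positive rate

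*Protocol article*

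**What the plan says.** Study design sets up a cluster trial "with schools as the unit of randomisation", "with 20 schools randomly allocated to the intervention group, and 12 to the control group".

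Under Statistical analysis, Demographic characteristics, two comparisons between arms are fixed:

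- Consent: "Intervention and control school parental consent rates will be examined for non-response bias using Chi square analysis".
- Demographics: "Intervention and control school student demographic characteristics will be compared at baseline and follow up also using Chi square analysis".

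Neither sentence mentions school. Clustering is handled in two other places. The Sample size section assumes "an intra-cluster correlation of 0.01", and Primary outcomes – substance use states: "For all outcome analyses, school will be included in the model as the clustering unit". Consent rates and demographics are not outcomes, so that sentence does not reach them.

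**The concern.** A chi-square test on student counts treats every student as an independent observation. Here whole schools were allocated, and students within a school may resemble one another in consent and in background. Any such resemblance makes the difference between arms vary more under the null than the test assumes, so its p-values are too small.

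The consent comparison is the plan's stated check for non-response bias. The trial needs active parental consent, and Random allocation of schools says that parents are not blinded to allocation, so a real difference in consent is a fair question. A test with the wrong error rate answers it badly: it can report differential consent, or different student populations, when all that was seen is ordinary variation between 20 schools and 12.

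**Working it through.** **Inputs from the protocol article**

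- Schools: 20 intervention, 12 control (Study design).
- Grade 7 students: 2,270 and 1,360, together 3,630; 3,630/32 = 113.4 per school (Sample size).
- Grade 10 students: 1,700 and 1,020; 1,700/20 = 1,020/12 = 85 per school (Sample size).
- ICC: 0.01, given for the substance-use outcomes (Sample size).
- Consent denominator: unclear. Student sample gives about 3,600 eligible students, or 3,600/32 = 112.5 per school. Sample size applies 80% consent before arriving at 3,630; on that reading 3,630/0.80 = 4,537.5 students were approached, or 141.8 per school. Both are carried through.

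**Step 1: the plan's own figures.** The design effect is DEFF = 1 + (m − 1) × ICC, with m students per school. For Grade 10 it is 1 + 84 × 0.01 = 1.84. The effective sizes are 1,020/1.84 = 554 and 1,700/1.84 = 924. Solving the two-proportion test (pooled variance, two-sided 5%, 80% power) gives these detectable differences in percentage points:

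| Outcome (control prevalence) | Stated | With DEFF 1.84 | Without DEFF |
|---|---|---|---|
| Smoking (14%) | 4.8 | 4.77 | 3.6 |
| Alcohol (36.2%) | 7.0 | 7.03 | 5.2 |
| Marijuana (25%) | 6.2 | 6.19 | 4.6 |
| Other illicit drugs (9.3%) | 3.9 | 3.88 | 3.0 |

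The stated figures reproduce only with the design effect, so the sample size does allow for clustering.

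**Step 2: the chi-square without that allowance.** Under the null, the unadjusted 1 df statistic is inflated by about DEFF. The actual error of a nominal 5% test is therefore 2 × [1 − Φ(1.96/√DEFF)]. For Grade 10 demographics, 1.96/√1.84 = 1.445, which gives 0.1485. All cases:

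| Comparison | m | DEFF at ICC 0.01 | Error at ICC 0.01 | Error at ICC 0.001 | Error at ICC 0.05 |
|---|---|---|---|---|---|
| Grade 10 demographics | 85 | 1.84 | 0.1485 | 0.0598 | 0.3901 |
| Grade 7 demographics | 113.4 | 2.124 | 0.1787 | 0.0631 | 0.4463 |
| Consent, 3,600 approached | 112.5 | 2.115 | 0.1778 | 0.0630 | 0.4447 |
| Consent, 4,537.5 approached | 141.8 | 2.408 | 0.2066 | 0.0665 | 0.4894 |

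Across the four rows, an ICC of 0.005 gives 10% to 13% and an ICC of 0.02 gives 23% to 32%. Only 0.01 stands in the protocol; the other ICCs are assumptions that show the range.

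**Step 3: check by simulation.** Beta-binomial data for 20 against 12 equal-sized schools at ICC 0.01 (40,000 runs per setting) gave 15.0% at 85 per school, 17.7% at 113, and for consent 17.8% at 113 and 20.7% at 142. This agrees with the formula.

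**Step 4: what restores 5%.** At ICC 0.01 the unadjusted statistic would have to exceed 3.84 × DEFF instead of 3.84: about 7.07 for Grade 10 demographics, 8.16 for Grade 7 demographics, and 8.1 to 9.25 for consent.

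**The case against.** The strongest reply is that the article does not say which chi-square is meant. A Rao-Scott test is a chi-square analysis, the article is condensed, and the clustering sentence does not say that it covers outcome analyses alone. The wording indeed does not exclude an adjusted test. But it names none, and the plan says so where it wants school in a model. An analyst who followed the text would run the unadjusted test.

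The second reply concerns size, and much of it stands:

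- No ICC is given for consent or demographics. Nothing in the document shows that they are strongly clustered. For age and gender this is not evident, since the cohort is a single grade and schools that are not co-educational are excluded.
- The formula is for 1 df and does not carry over directly to an item with many categories, such as postcode.
- Stratification by school size and by engagement in the national initiative could lower the inflation. Unequal school sizes could raise it.
- At ICC 0.01, some 79% to 85% of null comparisons would still be non-significant. The check can mislead, but it is not bound to.

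Third, these are supporting comparisons with no decision rule attached.

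**Conclusion.** The point holds as a fault in supporting analyses. As written, the comparisons of consent and demographics have an error rate above their nominal 5%: about 15% to 21% if the protocol's outcome ICC of 0.01 applies to them, and between 6% and 49% over assumed ICCs of 0.001 to 0.05. These figures rest on equal school sizes, 1 df, no gain from stratification, and a consent denominator that the article leaves open.

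A reader might infer two stronger things that the document does not support:

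- *That the primary result is compromised.* The primary GEE takes school as the clustering unit, and its inference does not depend on these tests. The plan mentions adjustment for potential confounders but nowhere says that chi-square p-values select them.
- *That the follow-up comparison is the trial's check on differential loss.* The article says only that demographics are compared between arms at that time and gives the comparison no such role.

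**What to change.** In Demographic characteristics, replace the chi-square tests of consent rates and demographics with a named cluster-adjusted method. Any of these would do: a Rao-Scott chi-square, a logistic GEE with school as the cluster and a small-sample variance correction, or a comparison of school-level rates across the 32 schools. Add that these p-values will not be used to choose covariates for the primary model. State the denominator for the consent rate, so that Student sample and Sample size agree.

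The cost is a few sentences and a different procedure call. No data collection or design feature changes. Leaving p-values out of the baseline table altogether is an optional preference and not part of this correction.
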